### Intervention

**
*HCD workshop procedure*.** In Phase 1, prior to the HCD process, an extensive desk review and secondary data analysis were conducted to identify key drivers of vulnerability affecting uptakes of maternal and child health services (ANC and institutional delivery). Vulnerability driving factors, such as women's illiteracy, distance from health facilities, high parity, decision-making power, exposure to media, and lack of household assets were identified as major barriers to maternal health service use. Based on these factors, a vulnerability screening tool was developed to identify the target population of rural vulnerable pregnant women. Couples who met three or more of the vulnerability criteria among those driving factors (e.g., living over 30 minutes from a health facility, being illiterate, having poor housing conditions, and lacking a mobile phone) were identified. From a desk review and evidence synthesis of secondary data, two initial design challenges focusing on ANC and institutional delivery were prioritized: 1) reimagining how to support pregnant women to attend ANC, and 2) reimagining how to support pregnant women to deliver in a health center. Then, an iterative five-phase design thinking process was implemented, including empathy, define, ideate, prototype, and testing that provides a flexible framework for co-creating solutions with community members and heath care stakeholders. 

The process involved a series of co-creation workshops in two rounds with diverse stakeholders. The initial round of workshops included pregnant women and husbands, organized as separate workshops to ensure open discussion. A total of eight teams (four teams of pregnant women and four teams of husbands) were organized in the two implementation woredas. A design team constituted up to six participants per concurrent session. Four teams focused on the design challenge on ANC, while the remaining focused on institutional delivery. These teams engaged in the empathy, design, and ideate phases of the HCD process. Subsequently, another set of workshops was conducted with healthcare providers (health development army, health extension workers, midwives/nurses, PHCU directors and woreda maternal and child health coordinators) organized into eight different teams: four on the first design challenge and four on the second. The second round of workshops was led by trained design workshop facilitators, building on the first-round outputs to ensure key insights from the teams of pregnant women and husbands were not lost. The mid-fidelity prototype solutions were tested with vulnerable pregnant women, husbands and community health workers to assess feasibility and acceptability. A total of 204 participants engaged in workshops and prototype testing. A core team of senior design staff further synthesized the outputs of the first and second round workshops. Insights around limited household support for pregnant women, low awareness on importance of healthcare services, demotivated healthcare providers, and poor service quality were harvested from these workshops.

**
*Development of HCD solutions*.** In the prototyping phase, our team prioritized potential prototype solutions based on an impact and feasibility matrix. The matrix served as a grading system to narrow down prototype solutions from those that were initially ideated among workshop participants based on the two dimensions: perceived impact (low or high) of solutions on institutional and ANC uptake and perceived feasibility (less or more likely to be implemented) pertaining to resource constraints. For example, while some solutions addressing structural-level factors, including transportation, were perceived as impactful, they were eliminated due to limited resources to address them.

Ultimately, three solutions were selected: a self-paced, audio-based program on ANC and health facility delivery to promote couple discussion on these issues, visual print materials reinforcing the audio content on ANC and institutional delivery, and home visits by health development armies (community health volunteers) to deliver these materials and provide interpersonal education to couples. Our final solutions primarily addressed individual and social-level factors, such as perceptions, knowledge, and social and gender norms, while also partially influencing service-level factors by improving service providers' perceptions and engagement.

The study team developed two pre-recorded audio programs containing real stories of pregnant women in the local language of the target area. The first audio session focuses on the importance of ANC through the narration of a couple's story, highlighting their communication and the husband's support in household tasks, as well as accompanying the wife to ANC visits. The second audio session focuses on the importance of institutional delivery from a story of a pregnant woman. It describes her first childbirth at home, which was a painful and difficult experience. The story then progresses to her second childbirth experience at a health facility, where she was well-prepared and supported by her husband. The two visual print materials (pamphlets) included graphics and text emphasizing behavioral action points that reinforced the audio messages. These prototypes were tested through focus group discussions with pregnant women, their husbands, healthcare providers and community volunteers, and then refined based on user feedback. Most responses were positive, with participants expressing appreciation for the relatable storytelling and the ease of engaging with the content at their own pace. Minor suggestions were received, primarily concerning the clarity of certain audio elements. Based on this feedback, minor adjustments were made to enhance the prototype’s usability and appeal. All five of the design thinking stages were implemented in the two study sites (Shalla and Siraro) of Oromia regional state.

For Phase 2, we aim to leverage implementation research data from Phase 1 to finalize our HCD plans and solutions. Learnings from Phase I indicated that the solutions significantly increased institutional delivery rates among vulnerable pregnant women. However, the production costs of the solutions, the intensity of implementation requiring close follow-up and supervision at health facilities, and challenges in ensuring health system ownership for scalability and sustainability were identified as major bottlenecks. Thus, HCD in Phase 2 will focus on the new design challenge: reimagining the couple communication-based interventions to enhance scalability and health system ownership, with the goal of increasing institutional delivery rates among vulnerable pregnant women.

We will apply the same five-stage HCD process in Phase 2. Since Phase 2 will focus on refining and strengthening the existing solutions, some of the HCD activities (e.g., “How Might We” statements and ideation) are expected to center around strategies for improving the materials and implementation delivery mechanisms through which scalability and health system ownership will be ensured. The HCD solutions will be tested with two target populations (pregnant women and implementers).

### Implementation plan

As part of the implementation of the interventions in Phase 1, the study team conducted an orientation training for health extensions workers and health development armies (known as Hadha Gare locally) to equip them with the skills needed to identify vulnerable pregnant women using a vulnerability screening tool and to effectively implement the solutions. The prototype solutions were delivered by the trained health development army with the help of health extension workers for a duration of four months from February to May 2024.

Prior to implementation, the health development army identified vulnerable pregnant women within their catchment area. They then scheduled an appointment to facilitate family discussions about the prototype solutions. The audio programs and print materials were intended to be delivered throughout five home visits by the health development army. For women whose gestational age was high (8–9 months), we aimed to provide audio and print materials on institutional delivery through three home visits.

In the first visit, the health development army provided the household with an audio device containing the pre-recorded ANC program and gave instructions on how to engage in couple communication around the program. After two to three days, the health development army revisited the household to inquire about questions or concerns from the couple, collected the device, and provided a print material to reinforce the audio content. The health development army then conducted a third visit to gather feedback from the couple and provided the second audio device that contained a story of institutional delivery. At the fourth visit, the health development army collected the second device and provided the second print material to reinforce institutional delivery messages from the audio program. Finally, the health development army conducted the final visit, encouraging the pregnant woman to utilize health services until she delivers and addressing remaining concerns among the couple. All of the home visits required the husbands’ presence given that the solutions were designed to facilitate couple communication, which would in turn optimize male involvement in maternal health service potentially through shifting social and gender norms. However, if the husband was not available for long durations during the implementation period, the health development army facilitated discussions with pregnant women and other family members.

To ensure seamless implementation of the interventions, the study team conducted close monitoring of activities that included site review meetings with implementing partners at the PHCU level and on-site supportive supervision to identify gaps, provide technical support, and address any identified implementation challenges. Key implementation outcome indicators, such as the number of pregnant women reached with ANC and institutional delivery audio programs and print materials, were regularly collected through the KoboCollect mobile platform.

### Data analysis plan

**
*Quantitative data analysis*.** First, we will conduct a series of bivariate tests, including chi-square and t-tests, across treatment and control arms based on baseline and endline data. The purpose of conducting bivariate tests is to identify differences between the study arms for each potential confounding factors, given the possibility of quasi-experimental design not ensuring baseline matching between intervention and control arms. If any differences are observed, they will be controlled for in subsequent regression analyses. We will also identify types of missing data to determine whether missingness occurs in a systematic manner, which will help us determine the appropriate remedial measure to adopt.

Since this project will conduct various implementation activities at the PHCU level, the analysis will take account of clustering at the level. Further, because
*kebeles* (akin to villages) are clustered within PHCUs, we will also consider clustering at the
*kebele* level. Given the nested nature of this study, multi-level modeling is considered appropriate because it provides both cluster-specific and population-averaged estimates simultaneously by defining both random effects and fixed effects, respectively. Prior studies that represented similar scenarios, however, have shown that estimated coefficients and standard errors are usually not biased, even with a sample size as low as 5 to 10 at Level 1
^
27,
28
^, and with many independent variables and interaction terms
^
29
^.

Nevertheless, this study will use a multi-level modeling framework to assess the intervention effect based on a difference-in-difference analysis by computing differences between baseline and midline within each arm, and then test this difference between intervention and control arms. A fixed effects model will first be used to observe this effect of the intervention. Kebele and PHCU will then be included as random intercepts to account for clustering within these levels. The estimated variance for random effects will show the amount of variability in the outcome that is explained by the clusters (i.e., how much of institutional delivery uptake is attributed to a kebele). If the coefficient of the interaction term is significant with the significant model fit, we will observe significant program effects. The identical analyses will be conducted with 4+ANC visits as the outcome variable. Other covariates will be included by comparing goodness-of-fit statistics (e.g., AIC, BIC) to improve the model fit. Proper model specification and diagnostic tests will be conducted to enhance the robustness of the results. Phase 2 data analysis will focus on comparing service utilization between intervention and control arms. Since we expect that study effectiveness will be stronger in Phase 2 with the implementation of enhanced solutions, we will also compare the study outcomes with baseline at Phase 1.

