### Data collection and measurement

**
*Survey interview*.** All participants from Phases 1 and 2 undergo a one-on-one survey interview to assess sociodemographic information, psychological factors, social and structural factors, and maternal health service utilization. A structured interview is administered by a local data collector in the local language. The survey captures the self-reported place of the most recent childbirth along with uptake and frequency of ANC visits during the most recent pregnancy. Secondary outcomes include knowledge, attitudes, and perceptions about maternal health service utilization, social norms, gender norms, spousal dynamics, decision-making, and community and structural factors. Midline (post-intervention in Phase 1) and end-line (post-intervention in Phase 2) assessments additionally include questions measuring program exposure.

**
*Qualitative interview*.** Purposively selected women from the study participants (n=20) along with health workers (n=32) engaged in the program participate in an in-depth interview. Given the 4-month duration of program implementation among pregnant women in their 5
^th^ or higher months of pregnancy, interviews are administered to recently delivered women inquiring about their perceived effects of the intervention on the place of childbirth and ANC uptake during pregnancy. Additionally, the interview guides for women and health workers contain questions around key implementation research outcomes, including acceptability and feasibility, to identify any similarities and differences arising across different types of interview participants.

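### The covariate-selection rule sets no limit to pre-intervention variables, so it could admit mediators measured after the intervention and attenuate the effect, chiefly in Phase 2

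*Protocol article*

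**What the plan says.** The quantitative part of the Data analysis plan selects covariates in two steps.

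- **Arm-difference screen.** The plan states that "we will conduct a series of bivariate tests, including chi-square and t-tests" will be run "across treatment and control arms based on baseline and endline data". The aim is to "identify differences between the study arms for each potential confounding factors", and the reason given is "given the possibility of quasi-experimental design not ensuring baseline matching between intervention and control arms". The consequence is fixed: "If any differences are observed, they will be controlled for in subsequent regression analyses". No significance threshold and no candidate list are given.
- **Fit criteria.** After the random intercepts for kebele and PHCU are described, the plan adds: "Other covariates will be included by comparing goodness-of-fit statistics (e.g., AIC, BIC) to improve the model fit".

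Two other sections bear on this. Data collection and measurement says: "Secondary outcomes include knowledge, attitudes, and perceptions about maternal health service utilization, social norms, gender norms, spousal dynamics, decision-making". The Intervention section says: "Our final solutions primarily addressed individual and social-level factors, such as perceptions, knowledge, and social and gender norms". The Implementation plan adds that couple communication is expected to raise male involvement by changing social and gender norms.

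Under Study design, Phase 1 surveys one panel at baseline and midline, while Phase 2 is a post-only comparison of the arms in a new sample.

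**The concern.** An arm difference found after the intervention can mean two things: the arms were never comparable on that variable, or the intervention changed it. Only the first calls for adjustment. In the second case the variable is a mediator, and conditioning on it takes out the part of the effect that runs through it. Neither a between-arm test nor AIC/BIC can tell the two apart. A mediator that works well will differ between arms and will predict the outcome, so it passes both steps.

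Testing on endline data also fails to serve the reason given for testing. If the question is whether the arms matched at baseline, an endline difference in a variable the intervention can alter does not answer it.

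Phase 2 has most at stake. Its women have no pre-intervention survey, no difference-in-difference contrast is available within that sample, and the woredas were not randomly selected. Covariate adjustment is then a main defence against confounding, so the choice of covariates matters.

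**Working it through.** **1. Could the rule admit these variables?** The protocol states no figure for covariate selection, so this step is a reading of the text.

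- The screen is confined to potential confounders, a term the article does not define.
- The Introduction lists social and gender norms and decision-making power among the barriers to service uptake. The Intervention section names decision-making power among the drivers of vulnerability. An analyst could reasonably call them potential confounders.
- The AIC/BIC step does not carry even that restriction.
- No sentence limits adjustment to variables measured before the intervention or unalterable by it.

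The rule therefore permits their entry. It does not require it.

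**2. The plan's own figure for the comparison most affected.** Sample size calculation gives 531 per arm in Phase 2 for a 9-point difference, 80% power and 10% non-response. Taking 48% against 57% and two-sided alpha 0.05 (sidedness is not stated):

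n = [1.960 × √(2 × 0.525 × 0.475) + 0.842 × √(0.48 × 0.52 + 0.57 × 0.43)]² / 0.09² = 483 per arm

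483 × 1.1 = 531.3, and 483 / 0.9 = 537. The stated 531 reproduces. The fix leaves it as it is.

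**3. What adjusting for a mediator would do (assumed inputs).** If a share s of the total effect runs through a score, the adjusted arm coefficient is approximately total × (1 − s):

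- s = 25%: 9 × 0.75 = 6.75 points
- s = 50%: 9 × 0.50 = 4.5 points

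A simulation checked this and also whether the rule would select the score. It used 531 women per arm, a 48% control rate, a 9-point total effect, a norms score shifted 0.4 SD by the intervention, linear probability models and 600 runs per scenario. The shift and the mediated shares are assumptions.

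| Share mediated | Unadjusted effect (points) | Adjusted effect (points) | Power unadjusted | Power adjusted |
|---|---|---|---|---|
| 25% | 9.1 | 6.8 | 0.86 | 0.57 |
| 50% | 9.0 | 4.5 | 0.83 | 0.31 |
| 75% | 8.9 | 2.2 | 0.84 | 0.10 |
| 100% | 8.8 | 0.1 | 0.81 | 0.05 |

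The arm test at 0.05 flagged the score in every run. That is expected: 0.4 / √(2/531) = 6.5 standard errors. AIC kept the score in 99% to 100% of runs in these four scenarios. The simulation has independent women, no confounding and one score measured without error, so it shows the mechanism and does not forecast the trial.

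**4. The screen in the other direction.** If the screen used two-sided 0.05 (assumed), a true imbalance of 50% against 57% would be missed about 66% of the time with 240 per arm and about 37% with 531 per arm.

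**The case against.** The defence has several good points.

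- **Norms and attitudes are never named as covariates.** The screen covers potential confounders only, and these variables are classed as secondary outcomes with their own study objective. A reader might infer that the plan will adjust away the attitudes and norms it means to change. The text does not say so. The absence of a covariate list is no error either, since an article may leave it to the full protocol or analysis plan.
- **Endline may mean only Phase 2.** The protocol calls the Phase 1 follow-up midline. On that reading Phase 1 is screened on baseline data and Phase 2 on the only survey it has. Endline reports of age, parity, literacy or distance are harmless there. This stands, and it is why the concern centres on Phase 2.
- **Phase 1 has other protection.** The difference-in-difference contrast deals with stable arm differences, so covariate choice is not the main safeguard in that phase.
- **The second step can rescue missed confounders.** AIC/BIC tends to keep strong predictors of the outcome even when the arm test misses them, so the 66% and 37% in the working describe the first step alone.
- **Inflated significance is not shown.** A reader might infer that p-values after such selection are too small. The arm term is not itself selected, the direction is not fixed in general, and attenuation would make p-values larger.

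None of this supplies the missing restriction. A stated rule that adjusts for any difference found, on data that include the post-intervention survey, still needs a sentence to keep mediators out.

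**Conclusion.** The concern holds as a weakness in a stated method. Selection by between-arm tests on baseline and endline data, followed by AIC/BIC, does not separate confounders from mediators, and nothing limits it to pre-intervention or unalterable variables. It could attenuate the estimated effect, chiefly in the Phase 2 arm comparison, and its use of endline data does not fit the stated purpose of checking baseline matching.

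The size is illustrative. About 6.8 to 4.5 points would remain of a 9-point effect if 25% to 50% of it ran through an adjusted score. Of these inputs only the 9 points comes from the protocol. The figure also presupposes that such a score enters the model, which the text allows but does not state. The rule should be corrected before Phase 2 is analysed.

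**What to change.** Replace both selection rules with one pre-specified adjustment set, the same for both outcomes and both phases, made up of variables the intervention cannot alter. Examples are age, parity (counted before the index birth), gestational age at enrolment, literacy or education, household assets, distance to facility, and near or remote woreda. Use baseline values in Phase 1 and endline reports of the same fixed characteristics in Phase 2.

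Two further candidates are conditional:

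- **Prior place of birth**, only if the survey records it separately from the index birth. The article mentions only the most recent childbirth, which after delivery is the outcome.
- **The vulnerability score**, only if it was taken before exposure. The tool includes social items, and Study design has Phase 2 women recruited after the refined solutions are implemented.

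Keep arm-comparison tables in both phases descriptive, with no role in choosing covariates. Analyse post-intervention knowledge, norms and decision-making only as outcomes or as mediators under the second evaluation objective.

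The cost is small: a few sentences in the analysis plan, the loss of data-driven selection, and possibly an added question on prior place of birth. The Phase 2 target of 531 per arm stands. Study status puts Phase 1 already in analysis and Phase 2 in preparation, so the set can be fully pre-specified for Phase 2. For Phase 1 the report should say when the set was fixed.

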**Figure 1. f1:**
[figure not shown]
Administration and health system structure in Ethiopia, adapted from the Federal Ministry of Health (FMOH).

Ethiopia's health system consists of three tiers: the primary tier includes one primary hospital, five health centers, and 25 health posts serving about 100,000 people; the secondary tier comprises general hospitals serving 1 to 1.5 million people; and the tertiary tier includes specialized hospitals serving 3.5 to 5 million people.

Our study sites are in Oromia, the most populous region in Ethiopia. Within this region, Siraro and Shalla woredas were selected as intervention arms, and Gera and Shebe woredas as control arms. The study sites were not randomly selected due to the on-going security issues in Ethiopia. The distance of woredas from major regional towns, maternal and child health service utilization (obtained from the national Health Management Information System data), and major livelihoods of the target study population were taken into consideration in the selection of intervention and control woredas. Two woredas (one nearby and one remote from towns) with similar health service uptake and predominantly agricultural livelihoods were assigned as the intervention group. The same strategies were used to select the control woredas. 

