### Sample size calculation

For Phase 1, we considered institutional delivery (a major outcome variable) as a basis for the sample size calculation. To estimate sample size, we took account of our longitudinal design that measures the same subjects before and after the intervention and assumed an intervention effect of 9% in improving institutional delivery beyond the current 48%
^
3
^. Assuming a p-value of 0.05, interclass correlation coefficient (ICC) of 0.009, a power of 80%, a total of 240 pregnant women from the intervention arm and another 240 pregnant women from the control arm are needed, for a total sample size of 480 pregnant women in each study phase. The assumptions of sample size also took into account feasibility and sample characteristics. The number of enumeration areas in the first phase was 80 per study arm, and approximately 5 women were expected to be eligible in each enumeration area. Based on the cross-sectional study design in Phase 2, we assumed 9% detectable difference between the study arms with an 80% power, which led to a sample of 531 for each study arm, taking account of 10% non-response rate. Approximately 106 enumeration areas will be reached from given the number of eligible women in each area. Both intervention and control arms will have an equal sample size in each phase, having 1:1 ratio of women between the intervention and control arms. As such, the total number of women to recruit across study arms in Phase 1 will be 1062.

For qualitative assessments, we use the same approach in Phase 1 and 2. An equal number of health workers (n= 32) are interviewed at mid-line (post-intervention of Phase 1) and end-line (post-intervention of Phase 2). The interviews with health workers explore the feasibility, acceptability, and scalability of the prototype solutions along with perceived program effects. The interviewees selected for Phase 2 may be the same service providers recruited from Phase 1 depending on their availability and engagement in the program. We have chosen 32 as the target sample size based on our best estimate about achieving data saturation. In each phase, we will also interview 20 pregnant women from the panel who recently delivered and were exposed to our HCD solutions. The qualitative interviews will be conducted only in the intervention sites.

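### The Level 1 reassurance about standard errors does not cover the Phase 2 arm comparison, which rests on the number of PHCUs within two non-randomised woredas per arm

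*Protocol article*

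**What the plan says.** All references are to the protocol article.

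The Data analysis plan recognises that women are clustered in kebeles and kebeles in PHCUs, and proposes multilevel models. It then offers a reassurance from prior studies: "estimated coefficients and standard errors are usually not biased, even with a sample size as low as 5 to 10 at Level 1". On the model itself it says "Kebele and PHCU will then be included as random intercepts to account for clustering within these levels". Woreda is not among the random terms.

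The detailed analysis that follows is the Phase 1 difference-in-difference between baseline and midline. For Phase 2 the section says only that service use will be compared between arms, with a further comparison against the Phase 1 baseline. Study design confirms that Phase 2 is post-only, in a new sample.

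Study setting assigns Siraro and Shalla to intervention and Gera and Shebe to control, and says the sites were not randomly selected. The number of PHCUs is not given. The nearest guide is the description of the primary tier: "one primary hospital, five health centers, and 25 health posts serving about 100,000 people".

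**The concern.** How many women there are per cluster and how many clusters there are per arm are separate questions. The first affects how well cluster-specific quantities are estimated. The second governs the standard error and degrees of freedom of any effect that is constant within clusters. In Phase 2, arm is such an effect: every woman in a PHCU, and every PHCU in a woreda, is in the same arm. A statement about Level 1 size therefore says nothing about whether the Phase 2 test keeps its error rate.

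Phase 1 is less exposed. There the same women are measured twice, and stable PHCU differences largely cancel in the difference-in-difference. A post-only comparison has no such cancellation.

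At stake is the Phase 2 effectiveness claim. With few PHCUs and a normal reference distribution, its error rate would exceed 5% and its confidence interval would be too narrow.

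**Working it through.** **Inputs from the article.** Sample size calculation, Phase 1: "Assuming a p-value of 0.05, interclass correlation coefficient (ICC) of 0.009, a power of 80"% and "assumed an intervention effect of 9% in improving institutional delivery beyond the current 48"%. Phase 2 takes a gap of 9 points at the same power; the resulting size is given in these words: "which led to a sample of 531 for each study arm, taking account of 10% non-response rate". The Phase 2 control rate and alpha are not restated, so I take 48% and two-sided 0.05.

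**1. The plan's own figure.** With pooled variance and no continuity correction,

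n = [1.96·√(2 × 0.525 × 0.475) + 0.8416·√(0.48 × 0.52 + 0.57 × 0.43)]² / 0.09² = (1.384 + 0.592)² / 0.0081 ≈ 482.1, so 483 per arm.

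483 × 1.1 = 531.3, which is the stated 531. With a design effect of 1 + (5 − 1) × 0.009 = 1.036, n would be 501, or 557 after dividing by 0.9. The Phase 2 size therefore matches a calculation with no clustering allowance, and it gives no hint of the PHCU count.

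**2. A rough floor for the PHCU count.** The Phase 2 plan reaches about 106 enumeration areas. Since 531/5 = 106.2, I read this as per arm. Study setting gives 750 to 1,000 people per area.

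- 106 × 750 = 79,500 and 106 × 1,000 = 106,000 people per arm.
- At five health centers per 100,000 people: 79,500 × 5/100,000 = 4.0 and 106,000 × 5/100,000 = 5.3, so about 4 to 5 catchments per arm.
- With the roughly three women per area given under Recruitment: 531/3 = 177 areas, 132,750 to 177,000 people, about 7 to 9 catchments.

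This treats one health center as one PHCU, which the article does not say. Scattered areas would touch more PHCUs, so the figures are floors.

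**3. True size of a nominal 5% z test with k PHCUs per arm, no between-woreda variance.** Size = 2·P(t > 1.96) on 2(k − 1) degrees of freedom. Interval widening is the t critical value divided by 1.96.

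| k per arm | df | size of z test | t critical value | ratio to 1.96 |
|---|---|---|---|---|
| 4 | 6 | 9.8% | 2.447 | 1.25 |
| 5 | 8 | 8.6% | 2.306 | 1.18 |
| 8 | 14 | 7.0% | 2.145 | 1.09 |
| 10 | 18 | 6.6% | 2.101 | 1.07 |
| 16 | 30 | 5.9% | 2.042 | 1.04 |
| 20 | 38 | 5.7% | 2.024 | 1.03 |

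**4. Check by simulation.** A logistic random-intercept model with 483 women per arm, PHCU ICC 0.009 and 2,000 runs per setting gave Wald z sizes of 8.8% (k = 5), 7.6% (k = 8), 6.8% (k = 12) and 4.2% (k = 20). Referring the same statistic to t gave 4.8%, 4.4%, 5.4% and 3.3%. With an assumed PHCU ICC of 0.05, z gave 12.6%, 9.6% and 7.8% at k = 5, 8 and 12, and t on the same model fit gave 7.5%, 6.6% and 6.4%. A t test on PHCU means (20,000 runs; k = 6, 10, 16) stayed at 4.8% to 5.2% at both ICCs.

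**5. If woredas also differ.** Two woredas per arm, PHCU ICC 0.009, k = 6 to 16, test on PHCU means. The woreda ICCs are assumptions, since the article gives none.

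| woreda ICC | z test | t test, PHCU df |
|---|---|---|
| 0 | 6.1–7.8% | 5.0–5.1% |
| 0.005 | 14.3–15.8% | 10.1–14.2% |
| 0.01 | 18.4–23.0% | 13.7–21.2% |
| 0.02 | 25.2–32.6% | 19.9–30.5% |

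Within each non-zero row the size rises with k: adding PHCUs inside the same four woredas does not help.

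**The case against.** The best defence has three parts.

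First, the article names no Wald z test, no maximum likelihood estimator and no degrees-of-freedom method. Such choices are commonly left to a statistical analysis plan, which is not at hand. This stands. A reader might infer that the Phase 2 test will be too liberal, but the document supports only the conditional: it would be, if a large-sample test were used and PHCUs were few.

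Second, few PHCUs is an inference. The health-center figure is per 100,000 people, not per woreda, and woreda populations are not given. This stands too, which is why the count is shown as a range. By 16 to 20 PHCUs per arm the excess is under one percentage point.

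Third, the sentence may answer a different worry. With three to five women per enumeration area, sparse clusters are a natural concern, and the text leads into the Phase 1 analysis. That is a fair reading of its purpose. It does not rescue the sentence as support for the plan's inference as a whole. It is the only assurance given about standard errors in the section that also covers Phase 2, and nothing there addresses the number of higher-level units.

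**Conclusion.** The point holds in a limited form. The Level 1 citation does not support inference on the Phase 2 arm effect. This is a misplaced argument in the text, not a detail left for later. Whether the test is actually liberal depends on facts not stated. With a z reference and no woreda variance, size runs from about 9.8% at 4 PHCUs per arm to 6.6% at 10 and 5.7% at 20.

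A reader might also conclude that a t test on PHCU degrees of freedom settles the matter at 5%. That is true only if the woredas do not differ. They were chosen, not randomised, and there are two per arm. Under the assumed woreda ICCs of 0.005 to 0.02, the PHCU-based t test still has a size of about 10% to 31%. The correction is worth making, but it removes only the part of the error that comes from the PHCU level.

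**What to change.** 1. Replace the Level 1 sentence with the number of PHCUs and kebeles expected in each arm.
2. Test the Phase 2 arm effect against a t reference with degrees of freedom based on the number of PHCUs, and report the matching interval. A PHCU-level summary analysis does this directly. A mixed model with a small-sample degrees-of-freedom correction is an alternative, but the 0.05 ICC simulation shows that swapping z for t without improving the variance estimate may not be enough.
3. State that two non-randomised woredas per arm limit inference, because between-woreda differences are not covered by PHCU-based degrees of freedom.

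The text change is a few lines. Intervals widen by about 7% at 10 PHCUs per arm, 18% at 5 and 25% at 4. Study status reports that Phase 1 data are being analysed and Phase 2 is in preparation, so this can be settled before Phase 2 outcome data exist.
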